### Randomization and blinding

2.9

An independent statistician, who is not be involved with the enrolment nor the assessment of the study participants, will establish and keep the concealed randomization schedule using a computer-generated random number sequence. The randomization sequence will be computed with the blocks of 4. Participants will be randomized into 2 groups with a ratio of 1:1, and the active and sham groups will be coded A and B, respectively. The code will be set in an opaque envelope and subsequently sealed. 10 tACS devices (5 sham and 5 active) have the same size, color, appearance, weight, and odor, and are coded as A or B. If one participant is allotted to A, only devices coded as A will be used through the course of the intervention, similarly if B, only B devices can be utilized. Two trained nurses of tACS devices will know the tACS devices’ status, but not involved in the assessment of participants and will keep blindness to participants and other study staff about tACS devices. Persons involving in the study, including the investigators, raters, EEG technicians, participants, trial monitors, and statistician, will be blinded to treatment assignment during double-blinded treatment until the end of follow-up.

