### The integrity of blinding

2.10

The integrity of trial-group blinding will be evaluated by asking participants and the blinded raters separately to guess which intervention each participant receives. Blinding will have to be broken in case of an emergency.

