### Sample size calculation

2.13

The sample size is estimated by assuming a 50% improvement rate at the end of 8 weeks in the active group and a 15% in the sham group, which were based on our pilot trial of the effect of tACS in adults with major depression disorder.^[38]^ Thus, each group will be recommended to have a minimum sample size of 26 with a power to 80% and a 2-tailed α level of 5%.^[53]^ Considering the 20% attrition rate, 32 evaluable participants will be required for each group. And the total sample size will be 70.

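### Two arm-wide device letters with a printed meaning (A active, B sham) let anyone who sees a participant's letter know that participant's arm

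*Protocol article*

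**What the plan says.** All of the coding scheme is in section 2.9 of the protocol article, Randomization and blinding.

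- Group code: "the active and sham groups will be coded A and B, respectively".
- Device code: "10 tACS devices (5 sham and 5 active) have the same size, color, appearance, weight, and odor, and are coded as A or B".
- Link between the two: "If one participant is allotted to A, only devices coded as A will be used through the course of the intervention", and the same for B.
- Concealment: "The code will be set in an opaque envelope and subsequently sealed".
- Who is blinded: investigators, raters, EEG technicians, participants, trial monitors and statistician "will be blinded to treatment assignment during double-blinded treatment until the end of follow-up". Two nurses know the device status, take no part in assessment and must keep it from the others.

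Section 2.5 gives each participant 20 sessions over four weeks, run by two trained nurses. Section 2.8 has two independent blinded raters assess participants at each time point. On unblinding, section 2.10 says only "Blinding will have to be broken in case of an emergency". It also plans to ask participants and raters to guess the allocation.

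**The concern.** Matching the devices in size, colour, appearance, weight and odour protects the blind only if nothing else about a device identifies the arm. Here the code letter does. It is common to everyone in an arm, and the protocol says what it means.

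The primary outcome is a response defined on HAMD-17, a scale scored by a rater, in a sham-controlled trial. If a rater or participant knows the arm, that knowledge can shift the score directly, and no analysis can remove the bias afterwards.

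**Working it through.** **1. From letter to arm.** Three statements in section 2.9 form a chain:

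- group A is active and group B is sham;
- every device carries A or B;
- a participant in group A uses only A devices, and likewise for B.

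So device letter = group letter = arm, with certainty. There are 2 codes for 10 devices and for 70 participants (section 2.13: "And the total sample size will be 70"), about 35 participants per letter at 1:1.

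**2. What one disclosure reveals.**

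| Event | Arms known with certainty |
|---|---|
| One letter seen, key printed (as planned) | 1, that participant's |
| k participants' letters held, key printed | k, up to 70 of 70 |
| One emergency unblinding, shared letters, key secret | 1, plus every other participant whose letter is held |
| One emergency unblinding, participant-specific codes | 1 |

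In the last row, an observer who also knew the block structure would guess correctly, on average, 1 + 3 × 2/3 + 66 × 1/2 = 36 of 70. Guessing alone gives 35. Participant-specific codes therefore confine a disclosure almost entirely to the one person concerned.

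**3. The fixed block size.** Section 2.9 states: "The randomization sequence will be computed with the blocks of 4". If an enroller knew every previous allocation in order, the six arrangements of AABB give:

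- Allocations known with certainty: two arrangements have 2 such positions and four have 1, so (2 × 2 + 4 × 1)/6 = 8/6 = 1.33 per block of 4 (33%). Over 70 participants (17 full blocks plus 2), 17 × 1.33 = 22.7, or 32%.
- Best guess, always naming the arm with fewer allocations so far: 17/6 = 2.83 correct of 4, or 70.8%. With the incomplete last block, this is 70.5% over 70 participants.
- The same strategy in blocks of 2, 4 and 6 gives 75.0%, 70.8% and 68.3%. Simulating 70 participants with the three sizes equally likely gives 70.1%.

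Varying the block size would therefore reduce the allocations known with certainty but leave the best-guess rate almost unchanged.

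**4. Effect on the sample size.** None. The coding scheme enters no power or sample-size figure.

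**The case against.** The strongest reply is that no section gives raters, investigators or participants access to the letters. The code is in a sealed opaque envelope. The sessions are run by two nurses who already know the device status, are kept away from assessment and must not disclose it. Separate blinded raters do the scoring, and section 2.10 would pick up some failures through the guessing question. This stands, and it makes the risk conditional. It does not remove it. The envelope and the nurses' discretion protect the letters but not the key, which is already printed. Participants attend 20 sessions with a lettered device, and the guessing question can detect a broken blind but cannot repair it.

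A reader might infer several stronger points that the documents do not support:

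- *One seen label exposes every allocation.* It exposes one. Reaching 70 of 70 requires someone who holds all the letters.
- *Emergency unblinding is the main danger.* With the key printed, an emergency adds nothing about what A means. The argument matters only if the key is made secret while the shared letters stay.
- *Blocks of 4 make allocation predictable.* The 33% and 71% hold only for someone who knows the previous allocations in order, and section 2.9 conceals the schedule and blinds the investigators.
- *The schedule holder is also the blinded statistician.* Section 2.9 has a statistician keep the schedule and lists a statistician as blinded; section 2.11 gives a statistician the final dataset and section 2.14 has a biostatistician analyse it. The text does not settle whether these are one person, and a full protocol would commonly say.
- *The blind is lifted before the data are clean.* Blinding to the end of follow-up does not say this, and the timing of database lock is commonly left to the full protocol or SAP.

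**Conclusion.** The point holds as a conditional weakness that should be fixed. Three facts are certain from section 2.9: the meaning of the letters is printed, only two letters serve all ten devices and all 70 participants, and a participant's letter fixes the arm. They sit badly with the blinding of participants, raters and investigators that the same section requires.

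The size is one arm revealed for each letter seen, up to 70 of 70 for someone holding every letter. How often a letter would be seen cannot be estimated from the article, so no figure can be put on the bias in HAMD-17 response. The conclusion assumes that the letters are legible on the devices or in opened envelopes, and that blinded people can read the protocol. With no documented route by which assessors see the letters, the safeguards in place keep this below a defect that would by itself invalidate the trial.

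**What to change.** Before the first participant is randomized:

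1. Remove the statement of which letter is active from the protocol.
2. Give the ten devices neutral individual numbers, or cover each label with a participant-ID sleeve, so that no arm-wide mark is visible.
3. Use participant-specific sealed envelopes naming the permitted device numbers, with the key held only by the schedule holder and the two unblinded nurses. The fewer numbers an envelope names, the less one disclosure spreads. With one device per participant, about 35/5 = 7 people share a number, whereas naming all five would recreate an arm-wide code. Sleeves avoid this altogether.

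The cost is relabelling ten devices, new envelopes, a short wording change and a small logistic burden for the nurses. No extra participants, visits or staff are needed.

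Varying, undisclosed block sizes are optional. They would reduce the allocations known with certainty but would not materially change the 71% best-guess rate.

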**Methods::**

The prospective study is an 8-week, double-blind, randomized, placebo-controlled trial. Seventy eligible participants with mild to moderate PSD aged between 18 years and 70 years will be recruited and randomly assigned to either active tACS intervention group or sham group. Daily 40-minute, 77.5-Hz, 15-mA sessions of active or sham tACS targeting the forehead and both mastoid areas on weekdays for 4 consecutive weeks (week 4), and an additional 4-week observational period (week 8) will be followed up. The primary outcome is the proportion of participants having an improvement at week 8 according to the Hamilton Depression Rating Scale 17-Item (HAMD-17) score, including the proportion of participants having a decrease of ≥ 50% in HAMD-17 score or clinical recovery (HAMD-17 score ≤ 7). Secondary outcomes include neurological function, independence level, activities of daily living, disease severity, anxiety, and cognitive function. The exploratory outcomes are gamma and beta-oscillations assessed at baseline, week 4, and week 8. Data will be analyzed by logistical regression analyses and mixed-effects models.

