### Intervention

2.5

Participants will be allotted to receive active or sham tACS intervention (Nexalin Technology, Inc., Houston, TX) under the same instructions during all sessions for 4 weeks in addition to their routine therapies (including antiplatelet, lipid-lowering, antihypertensive, or antidiabetic therapy). Two trained nurses will conduct the intervention and instruct participants to receive tACS. Participants will be encouraged to turn off their smartphones, drink water, and relax, even fall asleep. Communication with the trained nurses will be restricted.

Three electrodes will be positioned to the scalp: one 4.45 cm × 9.53 cm electrode will be placed over the forehead (Fpz, Fp1, and Fp2, in the 10/20 international placement system) and two 3.18 cm × 3.81 cm over the mastoid areas. Each participant will receive 20 sessions of intervention in 4 consecutive weeks at the fixed time frame once daily from Monday through Friday, with weekends off. Each session lasts 40 minutes with the default current level of 15-mA and a patented frequency of 77.5-Hz in the active group and no stimulation in the sham group. Then, patients will have another 4 weeks of follow-up.

Participants will be guided to refrain from any antidepressants for treating PSD during the study, and can willingly withdraw from this study at any time and choose any other medical treatments, such as antidepressants, when their depressive symptoms worsen.

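### The nurses who deliver treatment know which devices are active, and the A/B key is printed in the protocol: an avoidable route to performance bias on a rated mood outcome

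*Protocol article*

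**What the plan says.** The abstract gives the design: "The prospective study is an 8-week, double-blind, randomized, placebo-controlled trial".

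Section 2.5 (Intervention) says who treats: "Two trained nurses will conduct the intervention and instruct participants to receive tACS". Each participant has 20 weekday sessions of 40 minutes over four weeks. The setting is a "default current level of 15-mA and a patented frequency of 77.5-Hz in the active group and no stimulation in the sham group". Both arms receive the same instructions, and talk with the nurses is restricted.

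Section 2.9 (Randomization and blinding) describes the equipment: "10 tACS devices (5 sham and 5 active) have the same size, color, appearance, weight, and odor, and are coded as A or B". It assigns the letters: "the active and sham groups will be coded A and B, respectively". It ties participants to devices by letter: "If one participant is allotted to A, only devices coded as A will be used through the course of the intervention". It then says of the operators: "Two trained nurses of tACS devices will know the tACS devices’ status, but not involved in the assessment of participants". The nurses must keep device status from participants and other staff. The list of blinded roles that follows covers investigators, raters, EEG technicians, participants, monitors and the statistician. The nurses are not on it.

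Section 2.10 checks blinding by "asking participants and the blinded raters separately to guess which intervention each participant receives".

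**The concern.** The primary outcome (section 2.6.1) is HAMD-17 response or a score of 7 or less at week 8. This is a rated measure of mood, so it can respond to what participants expect and to how they are treated. Blinded raters protect the scoring. They do not protect what happens earlier, in sessions run by people who know the arm.

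Three routes are open:

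- **Expectation:** cues passed to participants, intended or not.
- **Care:** differences in attention, for example to electrode contact.
- **Retention effort:** section 2.4 ends participation after two consecutive missed sessions, and the nurses run every session, so effort to keep people attending could differ by arm.

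An arm difference produced in any of these ways could not be separated from an effect of stimulation. The knowledge that opens these routes also appears unnecessary on the protocol's own description of the devices.

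**Working it through.** The point rests on reading sections together. The plan attaches no figure to blinding, so there is none to reproduce.

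**1. Do the people who treat know the allocation?** Section 2.5 has two trained nurses conduct the intervention. Section 2.9 has two trained nurses of the devices who know device status. That they are the same pair is an inference, but the natural one. Their absence from the list of blinded roles agrees with it.

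**2. Does delivery require that knowledge?** Active or sham is a property of the device: 5 of each, matched on size, color, appearance, weight and odor. The device is chosen by the participant's letter and the current is a default level. On that description the operator needs only the participant's code. The article gives no reason for more. It also does not say that display, output or handling are identical, so a hidden technical reason cannot be excluded.

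**3. Would deleting the sentence about the nurses be enough?** No. Section 2.9 prints the key, and two letters cover all 10 devices. Anyone who has the protocol and knows a participant's letter knows the arm. Section 2.10 provides for emergency unblinding. With only two letters, one such event links a letter to an arm and so reveals the arm of every participant whose letter is known.

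**4. Exposure.** 20 sessions × 40 min = 800 min = 13.3 h per participant, for all 70. This is session time. It is not interaction time, which the document does not give.

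**5. Sensitivity to an operator effect (illustration only).** The document gives no size for such an effect, so b below is an assumption. The 15% and 50% rates are those of section 2.13; 35 per arm is 70 / 2, with no dropout. The test is the two-sided uncorrected chi-square at 5%.

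(a) No true effect, sham rate 15%, and an operator effect that adds b to the active arm. Rejection probability = sum over all (x₁, x₀) of Bin(x₁; 35, 0.15 + b) × Bin(x₀; 35, 0.15) × 1{|Z| > 1.96}, where Z is the pooled two-proportion statistic.

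| b | rejection probability |
|---|---|
| 0 | 5.3% |
| 5 points | 8.4% |
| 10 points | 17.6% |
| 15 points | 31.7% |

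(b) True rates of 50% and 15%, and an operator effect in the other direction, where nurses compensate sham participants and raise the sham rate to 0.15 + b. Power = Φ{[d√n − 1.96√(2p̄(1 − p̄))] / √(p₁(1 − p₁) + p₀(1 − p₀))}, with n = 35, √n = 5.916 and p₁ = 0.50.

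- b = 0: (2.071 − 1.298) / 0.614 = 1.257, power 89.6%.
- b = 5 points: (1.775 − 1.322) / 0.640 = 0.707, power 76.0%.
- b = 10 points: (1.479 − 1.342) / 0.661 = 0.207, power 58.2%.

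A shift of 5 to 10 points in either direction would therefore matter in a trial of this size. Nothing in the document says that such a shift will occur.

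**6. Effect of the fix on the sample size.** None. Masking the nurses alters no input to section 2.13.

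**The case against.** The strongest reply is that the protocol discloses a deliberate arrangement and limits its consequences. Much of that stands:

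- **The label.** A reader might infer that the trial is effectively open and that calling it double-blind is false. The document does not support this. Participants, raters and the other listed staff are to be blinded, and blinding of participant and assessor is an ordinary meaning of the term. Only the operators are unblinded.
- **The safeguards.** There are several: the same instructions in both arms, restricted communication, no role for the nurses in assessment, a duty not to disclose, two independent blinded raters (section 2.19's counterpart in this article is section 2.8), and staff training in communicating with participants (section 2.11). They reduce the risk. They do not remove knowledge of the arm from those who treat.
- **The guess check.** Leakage to participants or raters could show up as correct guesses, so it is wrong to say that nurse influence would go undetected. The check could not trace such leakage to the nurses, and it would miss differences in care or retention effort that change nobody's belief. Asking the nurses today would add nothing, because they already know.
- **The direction.** A reader might infer that any bias favours active tACS. The document does not show that. A nurse who knows that a participant is on sham might compensate with extra encouragement, which would narrow the contrast.
- **The printed key.** A reader might infer that the raters are unblinded by it. The document does not say that raters see the code letters.
- **Feasibility.** That operators could be masked is inferred from matched appearance and a default setting. A device feature that the article does not describe might prevent it.

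**Conclusion.** The point holds as a design weakness that should be corrected. It is not a contradiction in the plan, and it is not evidence that outcome rating is unblinded. Section 2.9 gives the operators knowledge of allocation, prints the key to it, and gives no reason, although the devices as described would let a nurse work from a code alone. This leaves an avoidable route for performance bias on a rated mood outcome in all 70 participants.

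The size and direction of any bias are unknown. The rejection and power figures above only show how sensitive a trial with 35 per arm would be to assumed shifts. The conclusion rests on two inferences: that the nurses of sections 2.5 and 2.9 are the same two people, and that no undescribed device feature forces disclosure.

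**What to change.** In section 2.9:

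- Delete the statement that the nurses know device status, and add the nurses to the list of blinded roles.
- Replace the published A/B key with a concealed one, preferably an individual code for each device, so that one emergency unblinding does not reveal every participant's arm.
- Name an independent code holder who neither treats, assesses nor analyses. Section 2.9 lists the statistician as blinded, so the analysing statistician should not hold the key.

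In section 2.10, once the nurses are masked, include them among those asked to guess.

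The cost is relabelling 10 devices, arranging custody of the code and rewording two sections. No participants or devices are added, and the sample size does not change.

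If a device feature makes operator masking impossible, say so and describe the trial, in the abstract and in section 2.9, as participant- and assessor-blind with unblinded operators.

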### The integrity of blinding

2.10

The integrity of trial-group blinding will be evaluated by asking participants and the blinded raters separately to guess which intervention each participant receives. Blinding will have to be broken in case of an emergency.

### Data monitoring

2.11

The trial will be performed according to the International Conference on Harmonization Guidelines for Good Clinical Practice to assure the rigor of the study. Data will be collected in the paper-based CRFs at baseline, weeks 4 and 8 (Table 1). An independent party approved by the local ethical committees will be responsible for data management. All staff is asked to join in a series of training sessions that will cover communicating with participants on trial, handling assessments, instructing participants to relax and drink water during the tACS intervention, collecting variables, and completing CRF. Data will be entered into the EpiData system by two independent investigators, and double-entry verification will be conducted. Any inconsistent entries will be re-checked with original CRF or investigators’ source data if necessary. Typos will be revised until two entered databases are the same. Auditing will be performed for the trial via frequent visits by two neutral trial monitors who have been appointed by the local ethics committee. The independent statistician will have access to the final trial dataset, including intent-to-treat dataset (i.e. all enrolled participants as belonging to the group they will be randomized into) and per-protocol dataset (i.e. those participants who will complete the trial originally allocated).

### Compliance and retention

2.12

For maximizing compliance and retention over the trial, the information on the entire trial (including the study schedule, requirements, potential risks, and benefits) will be fully explained to all interested participants. The signed informed consent form will be obtained before the initiation of tACS intervention. All patients will receive a call for their exact appointments before their assessments at weeks 4 and 8. Additionally, we will provide patients ongoing treatment regimens for their brain vascular diseases, free transportation allowance, and free relative examination. After the trial, we will continue to provide patients treatments for their vascular diseases in our outpatient clinic.

